## ***Randomisation Procedure***

Randomisation codes were produced by means of the PROC PLAN of the SAS system, with a 1:1 ratio of assignment between both arms, stratifying by centre, blocks multiple of 2 elements. The randomisation schedule will be managed from the eCRF in a concealed manner.

## ***Statistical analysis***

### ***Descriptive analysis***

A descriptive analysis will be performed for all parameters overall and by arm at every study time-point. Categorical parameters will be presented by means of frequencies and percentages. Continuous parameters will be summarized by means of the appropriate descriptive statistics (mean  $\pm$  standard deviation or median and interquartile range).

The efficacy and safety endpoints will be descriptively compared between study arms. Changes from baseline, when applicable, will also be summarized by study arm.

### ***Inferential analysis***

The inferential analyses will be limited to the efficacy variables, and the adverse events.

### ***Primary endpoint***

The primary endpoint is the proportion of patients progressing to severe respiratory failure (Brescia-COVID  $\geq 2$ ), ICU admission, or death. The proportion of patients with failure at day 7, will be estimated using a log-binomial regression model including stratification variables. In the unexpected event that the model does not fit, the Poisson regression model with long-link and robust variance estimator will be used instead.

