##### *Objectives and endpoints*

Table 1 - Objectives and endpoints

| OBJECTIVES                                                                                                                                                                     | ENDPOINTS AND OUTCOME MEASURES                                                                                                                                                                 |
|--------------------------------------------------------------------------------------------------------------------------------------------------------------------------------|------------------------------------------------------------------------------------------------------------------------------------------------------------------------------------------------|
| PRIMARY                                                                                                                                                                 |                                                                                                                                                                                                |
| Evaluate the efficacy of an early intervention with sarilumab in COVID-19 infected patients with pneumonia and regular oxygen supplement requirements (Brescia-COVID 1) | The primary endpoint is the proportion of patients progressing to severe respiratory failure (Brescia-COVID $\geq 2$ ), ICU admission or death from randomization up to day 15th of follow-up. |
| SECONDARY                                                                                                                                                               |                                                                                                                                                                                                |

---

**Evaluate effects of efficacy of an early intervention with sarilumab on secondary efficacy endpoints as compared to standard of care as assessed by:**

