## 5. DESIGN OF THE STUDY

This is an exploratory phase II, multicenter, open-label, randomized clinical trial to evaluate the efficacy and safety of an early intervention with sarilumab + methylprednisolone (or equivalent CS dose) plus SOC vs methylprednisolone (or equivalent CS dose) plus SOC alone in patients with COVID-19 pneumonia aimed to prevent progression to severe respiratory failure, ICU admission, or death.

Experimental arm: Sarilumab + methylprednisolone (or equivalent CS doses) plus SOC for COVID-19

Control arm: methylprednisolone plus SOC for COVID-19.

Sarilumab will be administered intravenously following this posology:

-Patients <75kg body weight: single 200mg SARILUMAB dose (1 single-dose pre-filled syringe containing 200 mg sarilumab in 1.14 ml solution (175 mg/ml) added to 100 mL 0.9% sodium chloride for a 1-hour intravenous infusion).

-Patients ≥75kg body weight: single 400mg SARILUMAB dose (2 single-dose pre-filled syringes, each containing 200 mg sarilumab in 1.14 ml solution (175 mg/ml) added to 100 mL 0.9% sodium chloride for a 1-hour intravenous infusion).

Corticosteroids will be given to all patients at a 1mg/kg/d of methylprednisolone (or equivalent CS dose) for at least 3 days.

SOC includes [esing](#) weight adjusted corticosteroid doses plus any drugs that are being used in clinical practice (e.g. lopinavir/ritonavir; hydroxy/chloroquine, and other than those used as part of another clinical trial

Randomization will be 1:1 to any of the treatment groups and will be stratified per center.

For patients on will be rescued with sarilumab at the same doses and be included in a 15-day open-label follow up phase or until hospital discharge, ICU admission or death.

Clinical follow-up visits will be performed at 3, 5, and 15 days after treatment randomization.

Patients in any treatment group progressing to severe respiratory failure fulfilling criteria for treatment with anti-IL6 inhibitors according to clinical practice guidelines, as defined by the presence of Brescia-COVID 2-3 plus inflammatory markers, will be considered treatment failures for the sake

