#### *Efficacy assessments: follow up visits*

Clinical follow-up visits will be performed at 3, 5, and 15 days after treatment randomisation. Patients in SOC group without sarilumab progressing to severe respiratory failure fulfilling criteria for treatment with anti-IL6 inhibitors according to clinical practice guidelines, as defined by the presence of Brescia-COVID 2-3 plus inflammatory markers, will be rescued with sarilumab at the same doses and be included in an open-label phase. This group of patients will be followed up by two additional weeks after receiving sarilumab as rescue medication (days 3, 5 and 15 following sarilumab administration).

Patients randomly assigned to sarilumab therapy at baseline progressing to Brescia-COVID 2-3 will be rescued according to local clinical practice protocols.

For all patients a final follow-up visit is planned at D28 from randomization, regardless of the initial treatment assigned.

The following outcomes should be assessed:

- Hospitalization.
- ICU admission
- Hospital discharge
- Oxygen requirements.
  - Oxygen mask with reservoir bag.

- Non-invasive mechanical ventilation (via mask) or high flow oxygen nasal tubes
  - Mechanical ventilator requirement (via endotracheal tube or tracheostomy tub).
  - ECMO requirement.
- Ordinal scale score:
  1. Not hospitalized, no limitations on activities.
  2. Not hospitalized, limitation on activities.
  3. Hospitalized, not requiring supplemental oxygen.
  4. Hospitalized, requiring supplemental oxygen.
  5. Hospitalized, on non-invasive ventilation or high flow oxygen devices or oxygen mask with reservoir bag.
  6. Hospitalized, on invasive mechanical ventilation or ECMO.
  7. Death.
- PaO2/FiO2 Index or SpO2/FiO2 Index.
- Temperature °C
- Chest radiography (at least one during the follow-up period, recommended between D3-5, unless medically indicated any other day as part of the routine care)
- Laboratory disease parameters (CRP, d-dimer, IL-6, LDH, lymphocyte counts, ferritin, plus any routing laboratory determinations usually performed by the patients's physicians)
- Death.
- Concomitant medications
- Brescia-COVID score

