## **Study outcomes**

### *Primary Endpoint*

The primary endpoint is the proportion of patients progressing to severe respiratory failure (Brescia-COVID  $\geq 2$ ), ICU admission, or death.

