### ***Sample size estimation***

To obtain a power of 80.00% to detect differences in the contrast of the null hypothesis  $H_0: p_1 = p_2$  by means of a bilateral Chi square test for two independent samples, taking into account that the level of significance is 5.00%, and assuming that the proportion in the Reference group is 25.00%, the proportion in the Experimental group is 10.00%, and that the proportion of experimental units in the Reference group with respect to the total is 50.00 % it will be necessary to include 100 experimental units in the Reference group and 100 units in the Experimental group, totalling 200 experimental units in the study.

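### The primary endpoint is defined up to day 15 but analysed at day 7, a day with no scheduled Brescia-COVID score in the randomised phase, and the planning rates are tied to no day

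*Protocol*

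**What the plan says.** Four places in the protocol state the primary endpoint, and they do not agree on its time frame.

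- Section 4, Table 1: the composite of Brescia-COVID ≥2, "ICU admission or death from randomization up to day 15th of follow-up".
- Section 10, Primary endpoint, the only description of the primary analysis: "The proportion of patients with failure at day 7, will be estimated using a log-binomial regression model including stratification variables".
- Section 8, Primary Endpoint: "The primary endpoint is the proportion of patients progressing to severe respiratory failure (Brescia-COVID" ≥2), ICU admission or death, with no day.
- Synopsis, primary measure and endpoint: the same composite, again with no day.

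On timing of assessment, Section 5 states: "Clinical follow-up visits will be performed at 3, 5, and 15 days after treatment randomization". Section 8 repeats those days and adds a last contact: "For all patients a final follow-up visit is planned at D28 from randomization, regardless of the initial treatment assigned". The schedule of activities (Table 2) has columns for screening, baseline, 72 hours, day 5, day 15 (+2) and day 28 (±2). Its Brescia-COVID row is marked from screening to day 15 and is blank at day 28.

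The sample size paragraph in Section 10 proceeds by "assuming that the proportion in the Reference group is 25.00%, the proportion in the Experimental group is 10.00"%, with two-sided 5% significance, 80% power and 1:1 allocation, giving 100 per arm. Neither this paragraph nor its counterpart in the synopsis says at which day those proportions apply.

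Section 5 also says that patients who progress and meet the rescue criteria, "as defined by the presence of Brescia-COVID 2-3 plus inflammatory markers, will be considered treatment failures for the sake" of the primary analysis.

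**The concern.** Anyone following Section 10 as written would analyse a different endpoint from the one defined in Table 1. Patients who first progress, enter ICU or die between day 8 and day 15 are failures under Table 1 and non-failures under Section 10.

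The trial is open-label, and Section 8 leaves the timing of interim and final analyses to the principal investigator. Two candidate windows in the same document mean that two primary results could be produced from the same data, with the choice made after they are seen.

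Day 7 also fits poorly with the data to be collected. A patient scored 1 on day 5 and 2 on day 15 has no day-7 Brescia-COVID status from the scheduled scores alone.

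Finally, the 80% power claim belongs to one pair of rates. Unless failure rates are the same at day 7 and day 15, it cannot hold at both.

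**Working it through.** **Reproducing the planned sample size.** Inputs from Section 10, Sample size estimation: p₁ = 0.25, p₂ = 0.10, two-sided α = 0.05 (z = 1.960), power 0.80 (z = 0.842), 1:1 allocation, chi-square test. With pooled variance under the null and no continuity correction, p̄ = 0.175 and

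n = [1.960·√(2·0.175·0.825) + 0.842·√(0.25·0.75 + 0.10·0.90)]² / 0.15²

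= (1.053 + 0.443)² / 0.0225 ≈ 99.5, rounded up to **100 per arm**. This matches the protocol.

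Power at n = 100 is Φ{[0.15·√100 − 1.053] / 0.527} = Φ(0.848) = 0.802. The arithmetic is sound; what is missing is the day to which 25% and 10% refer.

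**Assumption A: 25%/10% are day-15 rates.** Suppose a fraction f of events in each arm has occurred by day 7. The day-7 rates are then 0.25f and 0.10f, and the same formulas give:

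| f | Day-7 rates | Power, 100 per arm | n per arm for 80% |
|---|---|---|---|
| 0.5 | 12.5% / 5.0% | 0.47 | 222 |
| 0.6 | 15.0% / 6.0% | 0.55 | 181 |
| 0.7 | 17.5% / 7.0% | 0.62 | 152 |
| 0.8 | 20.0% / 8.0% | 0.69 | 131 |
| 0.9 | 22.5% / 9.0% | 0.75 | 114 |

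Under constant hazards, p(7) = 1 − (1 − p(15))^(7/15). This gives 12.6% and 4.8%, power 0.50, and 206 per arm for 80%.

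**Assumption B: 25%/10% are day-7 rates.** Under constant hazards, p(15) = 1 − (1 − p(7))^(15/7). This gives 46.0% and 20.2%, and power at day 15 is 0.98.

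**Matching the candidate days to the schedule.**

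| | Day 7 | Day 15 |
|---|---|---|
| Randomised-phase visit (Sections 5 and 8, Table 2) | none | yes |
| Scheduled Brescia-COVID score | none | yes |
| Table 1 primary endpoint | no | yes |
| Secondary endpoints using that day (ordinal-scale progression, 15-day mortality, organ failure) | none | yes |

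Table 2 gives no window around the day-5 visit. The ±1 day shown for day 5 in the rescue schedule (Table 3) would reach only day 6.

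**The case against.** A separate SAP is foreseen, and a time point might be thought its business. It is not here, because the protocol already states two different days.

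The stronger objection is that day 7 is workable. Deaths and ICU admissions carry dates. Time to progression to severe respiratory failure is a secondary endpoint, with Kaplan-Meier and Cox methods specified for survival endpoints, so dated progression is presupposed. Controls rescued with sarilumab are also scored on the day of rescue. This stands: a reader might infer that a day-7 result cannot be obtained at all, and the documents do not support that. What they show is narrower, namely that the Brescia-COVID component has no planned day-7 assessment in the randomised phase.

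Four other inferences also go too far:

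- **No day-7 visit anywhere.** Section 5 does name one, but it is counted from rescue in control patients who have already progressed. Section 8 and Table 3 give day 5 instead. It cannot supply the primary outcome.
- **A second, narrower failure definition.** The sentence in Section 5 about inflammatory markers can be read as one sufficient condition for failure, since those patients are a subset of Brescia-COVID ≥2. It is an ambiguity to reconcile, not a proven conflict.
- **Status on a day versus cumulative failure.** The sentence before the day-7 sentence in Section 10 speaks of patients progressing, which favours a cumulative reading.
- **Missing day-7 scores become failures.** The missing-data sentence seems to intend this, but its wording is garbled, so it cannot be taken as settled.

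A reader might also infer that the trial is underpowered. That follows only if the planning rates are day-15 rates and day 7 is analysed. Under the opposite assumption power rises.

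**Conclusion.** The contradiction is real and lies in the current text: the endpoint is defined up to day 15 and its only stated analysis is at day 7. The two remaining statements of the endpoint do not settle it, and neither does the sample size paragraph. It should be corrected before outcome data are reviewed, because the primary result is otherwise not uniquely defined.

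The effect on power depends on assumptions. If the planning rates refer to day 15, a day-7 analysis has power of about 0.47 to 0.75 when 50% to 90% of events fall by day 7 in both arms, against the planned 0.80. If they refer to day 7, day-15 power is about 0.98 under constant hazards. The documents do not show which day the rates describe or which day was intended for the analysis. Day 15 is the better-supported choice because it agrees with Table 1, the Brescia-COVID schedule and the day-15 secondary endpoints.

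**What to change.** 1. Use one time point in the synopsis, Section 4 Table 1, Section 8 (Primary Endpoint) and Section 10 (Primary endpoint). In Section 10, replace the day-7 wording with cumulative failure (first Brescia-COVID ≥2, ICU admission or death) from randomisation up to day 15. The sponsor should confirm that this is the intent before any outcome data are reviewed.
2. In the sample size text of the synopsis and Section 10, state which time point the 25% and 10% refer to and on what basis. If it is not the chosen day, restate the power.
3. Add a CRF field for the date of first Brescia-COVID ≥2. This is needed for the day-15 version too, since no score is scheduled between day 5 and day 15.
4. Make any day-7 analysis secondary and build it from dated events.
5. Reconcile the Section 5 failure wording that mentions inflammatory markers with the endpoint definition.

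The cost is wording changes in several sections and one CRF date field. No extra patients or visits are needed.

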#### ***Screening and Inclusion (Visit -1)***

Patients will be screened in the hospitalization ward by the investigators of the trial. Screening will take place within 1 day of selection, and administration of the first dose of sarilumab will be done within the following 24 hours. Screening will be preceded by a presentation of the complete information about the clinical study to the subject or family member by the investigator followed by signature of the informed consent form or by obtaining oral consent.

After the informed consent, all the following assessments are performed to determine eligibility requirements as specified in the inclusion and exclusion criteria and before the patient receives any study medication:

- Positive SARS-CoV-2 test result. Laboratory-confirmed SARS-CoV-2 infection as determined by PCR in naso/oropharyngeal swabs or any other relevant.

-Focused medical history, including the following information:

- Patient demographic characteristics: age, sex, race
- History of relevant chronic medical conditions and concomitant medications
- COVID-19 history: date of confirmation of disease, disease duration, fever, cough, other related symptoms.
- COVID-19 background medication: Corticosteroids, retrovirals, Hidroxychloroquine, etc.

-Focused physical examination: including vital signs, weight, auscultation, signs of respiratory distress, and any other as clinically indicated

-Oxygen supplement requirements: type and FiO2

-Oxygen parameters: SaO2, PaO2 (if available), SaO2 or PaO2/FiO2 Indexes

-Review recent radiographic imaging (x-ray or CT scan), valid up to 96h prior to randomisation.

-Laboratory disease parameters (IL-6, LDH, d-dimer, CRP, BUN, Ferritin, total white blood cell and total lymphocytes count, platelets count, and liver enzyme studies), valid within 24h prior to randomization

-Optional blood samples will be collected at baseline for future pharmacogenomic exploratory research\*

-Pregnancy Test (Pregnancy test in women of childbearing potential)

-Brescia-COVID Scale, CURB-65

-Adverse events

The overall eligibility of the subject to participate in the study will be assessed once all screening values are available. The screening process can be suspended prior to complete assessment at any time if exclusions are identified by the study team. Study subjects who qualify will be immediately randomized and treatment should be administered within 24 hours after randomization.

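### The primary model adjusts for centre only; prespecifying age and baseline oxygenation, with a model that can carry them, could add modest power at little cost

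*Protocol*

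**What the plan says.** Protocol section 10, Primary endpoint, states that the proportion of failures "will be estimated using a log-binomial regression model including stratification variables". It names a fallback: "In the unexpected event that the model does not fit, the Poisson regression model" with a robust variance.

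The stratification variables are settled elsewhere. Randomisation Procedure describes "stratifying by centre, blocks multiple of 2 elements", and the synopsis, the design section and Method of Treatment Assignment name no other factor. The primary covariate set is therefore centre and nothing else. The binary secondary outcomes inherit the same model.

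Section 8, Screening and Inclusion, lists what is recorded before treatment: "Patient demographic characteristics: age, sex, race" and "Oxygen parameters: SaO2, PaO2 (if available), SaO2 or PaO2/FiO2 Indexes", together with the type of oxygen support and FiO2. SpO2 and FiO2 are taken again just before dosing (Randomisation and Treatment). Only PaO2 depends on availability.

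**The concern.** Adjusting for pre-treatment values that predict the outcome improves precision and protects against a chance imbalance in severity. Both matter with 100 patients per arm and a sample size that has no margin. Here the values are already scheduled, so leaving them out saves no data collection.

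Severity at entry may well vary. The objectives target Brescia-COVID 1, but inclusion criterion 4 accepts radiographic infiltrates alone, so a patient on ambient air (score 0) can qualify. Exclusion criterion 1 removes reservoir masks, high flow and ventilation, but not a patient on ordinary oxygen with dyspnoea, which Appendix 6 scores as 2. The endpoint is defined on that same scale.

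The protocol accepts the principle elsewhere: its mixed models for continuous outcomes include the baseline measurement. In an open-label trial, covariates are also better named in advance than chosen once data have been seen.

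**Working it through.** **1. The plan's own figure.** Sample size estimation sets out "To obtain a power of 80.00% to detect differences" "by means of a bilateral Chi square test for two independent samples", where "the level of significance is 5.00"%, with 25% versus 10% and 1:1 allocation. With pooled variance, p̄ = 0.175:

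n per arm = [1.960·√(2·0.175·0.825) + 0.842·√(0.25·0.75 + 0.10·0.90)]² / 0.15² = (1.053 + 0.443)² / 0.0225 ≈ 99.5, so 100.

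Power at 100 per arm = Φ[(0.15·√100 − 1.053)/0.527] = Φ(0.848) = 80.2%. The figure reproduces with no covariate.

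**2. Events.** 100 × 0.25 + 100 × 0.10 = 35 expected.

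**3. Gain from adjustment.** Simulated trials of 200 patients, 2,000 per cell, with 25% versus 10% marginal risks. Assumed: 5 or 10 equal centres without centre effects, and two independent normal covariates with the same odds ratio (OR) per SD. Power (%) by robust Poisson, centre only → centre plus two covariates:

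| OR per SD | AUC, control arm | 5 centres | 10 centres |
|---|---|---|---|
| 1.0 | 0.50 | 78.6 → 78.7 (+0.1) | 78.6 → 78.4 (−0.2) |
| 1.3 | 0.60 | 79.8 → 80.2 (+0.4) | 79.5 → 79.2 (−0.3) |
| 1.5 | 0.65 | 78.2 → 79.6 (+1.4) | 80.4 → 81.4 (+1.0) |
| 2.0 | 0.74 | 80.3 → 83.8 (+3.5) | 78.9 → 81.4 (+2.5) |
| 2.5 | 0.79 | 78.6 → 84.4 (+5.8) | 79.6 → 83.5 (+3.9) |

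Each power figure has a standard error of about √(0.8·0.2/2000) = 0.9 points. Differences in starting power between rows are noise, so rows should be read across.

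**4. Repeat runs with a second method.** Gain over centre-only robust Poisson, in points (5 centres; 10 centres):

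| OR per SD | Robust Poisson with covariates | Standardised logistic |
|---|---|---|
| 1.0 | −0.2; 0.0 | +1.1; +0.7 |
| 1.5 | +2.0; +0.8 | +3.7; +2.1 |
| 2.0 | +3.4; +4.4 | +5.6; +5.9 |
| 2.5 | +5.7; +4.2 | +7.8; +6.5 |

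The standardised estimate gains about 1 point even when the covariates are uninformative, so that part comes from the method. Subtracting the OR 1.0 row leaves +2.6 and +1.4 at OR 1.5, +4.5 and +5.2 at OR 2.0, and +6.7 and +5.8 at OR 2.5. A further set of runs of the same design allowed a loss of up to about 2 points with uninformative covariates.

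**5. Type I error.** In the runs of step 3 under the null with 5 centres, it went from 5.1% to 5.4% (OR 1.0) and from 4.9% to 5.6% (OR 2.0). Across all checks the adjusted methods stayed at about 4 to 7%, with a standard error of about 0.5 points.

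**6. Can the named model carry the covariates?** Share of 300 simulated trials in which the log-binomial fit failed (%), centre only / centre plus two covariates:

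| OR per SD | 5 centres | 10 centres |
|---|---|---|
| 1.0 | 0 / 4.3 | 17.0 / 30.3 |
| 1.5 | 0.3 / 48.3 | 20.7 / 68.7 |
| 2.0 | 0 / 84.7 | 21.3 / 90.7 |
| 2.5 | 0 / 93.0 | 18.7 / 93.7 |

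The centre-only failures match the share of trials in which some centre had no event. These rates depend on the fitting algorithm.

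**The case against.** The strongest reply is that nothing here is wrong. Adjusting for the stratification factor matches the randomisation, is prespecified, and delivers the stated power. The protocol calls its text a summary and announces a detailed SAP, which may add covariates. This stands, and it limits the point to an improvement.

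A reader might infer that the plan gives away a known amount of power. The documents do not support that: they report no association of age or oxygenation with progression, and for weak covariates the gain is near zero. The Brescia-COVID 1 target also narrows the spread of oxygenation, although the entry criteria do not fully enforce it.

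A reader might also infer that the change is free, or that the covariates can simply be added to the log-binomial model. Step 6 shows otherwise: failures are most frequent where the gain is largest, so the fallback, which the protocol treats as unexpected, would become routine. This objection stands against keeping the log-binomial model. It does not stand against adjusting by robust Poisson or a standardised logistic estimate.

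Finally, the screening list gives a choice of oxygenation measures, and the SpO2/FiO2 index is named only for follow-up. It can be derived from values recorded before dosing, but this should be written down.

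**Conclusion.** The point holds as an efficiency improvement. The primary model ignores baseline prognostic values that the trial already collects, and prespecified adjustment is worth adopting. The expected gain is about 0 to 1.5 points of power at an odds ratio of 1.5 per SD or less (single runs reached 2.0, or 2.6 net for the standardised estimate), and about 3 to 7 points at 2 to 2.5 per SD for both covariates. The downside is a loss of about 0 to 2 points if the covariates are uninformative. These sizes rest on assumed prognostic strength, 5 or 10 equal centres and independent normal covariates; none can be read from the protocol. The plan is neither invalid nor short of its stated power.

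**What to change.** In section 10, Primary endpoint, replace the reference to stratification variables by a named list: centre, age and baseline SpO2/FiO2, the last derived from the values recorded before dosing. Name one primary method that tolerates continuous covariates. This can be Poisson regression with log link and robust variance, already the fallback, or a standardised (marginal) risk ratio from a logistic model with the same terms and a stated variance estimator. Keep the centre-only model as a sensitivity analysis. Add a simple rule for a missing baseline value, and one for centres without events, which already affect the centre-only model.

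The cost is a short edit and a change of model away from log-binomial. It needs no new data, visits or patients, and should be settled before outcome data by arm are examined.
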